# SWIVIT - Swiss video-intubation trial evaluating video-laryngoscopes in a simulated difficult airway scenario: study protocol for a multicenter prospective randomized controlled trial in Switzerland

**DOI:** 10.1186/1745-6215-14-94

**Published:** 2013-04-04

**Keywords:** Video-laryngoscope, Difficult airway, Airtraq, A. P. Advance, C-MAC, Glidescope, King vision, Mcgrath

## Abstract

**Background:**

Video-laryngoscopes are marketed for intubation in difficult airway management. They provide a better view of the larynx and may facilitate tracheal intubation, but there is no adequately powered study comparing different types of video-laryngoscopes in a difficult airway scenario or in a simulated difficult airway situation.

**Methods/Design:**

The objective of this trial is to evaluate and to compare the clinical performance of three video-laryngoscopes with a guiding channel for intubation (Airtraq™, A. P. Advance™, King Vision™) and three video-laryngoscopes without an integrated tracheal tube guidance (C-MAC™, GlideScope™, McGrath™) in a simulated difficult airway situation in surgical patients. The working hypothesis is that each video-laryngoscope provides at least a 90% first intubation success rate (lower limit of the 95% confidence interval >0.9). It is a prospective, patient-blinded, multicenter, randomized controlled trial in 720 patients who are scheduled for elective surgery under general anesthesia, requiring tracheal intubation at one of the three participating hospitals. A difficult airway will be created using an extrication collar and taping the patients’ head on the operating table to substantially reduce mouth opening and to minimize neck movement. Tracheal intubation will be performed with the help of one of the six devices according to randomization. Insertion success, time necessary for intubation, Cormack-Lehane grade and percentage of glottic opening (POGO) score at laryngoscopy, optimization maneuvers required to aid tracheal intubation, adverse events and technical problems will be recorded. Primary outcome is intubation success at first attempt.

**Discussion:**

We will simulate the difficult airway and evaluate different video-laryngoscopes in this highly realistic and clinically challenging scenario, independently from manufacturers of the devices. Because of the sufficiently powered multicenter design this study will deliver important and cutting-edge results that will help clinicians decide which device to use for intubation of the expected and unexpected difficult airway.

**Trial registration:**

NCT01692535

## Background

Difficult airway management remains a cornerstone of clinical anesthesiology. Difficulty in tracheal intubation is the most common factor related to serious airway complications during general anesthesia [1]. Recently, the combination of the fiberoptic bronchoscope and the laryngoscope led to the development of video-laryngoscopes, providing a video-based view of the glottic opening, with or without additional guidance of the tube towards the tracheal opening. Six devices are under prominent focus in recent publications.

1) The Airtraq (Prodol Meditec SA, Vizcaya, Spain) was the first video intubation device that featured a channel guiding the tube towards the tracheal opening. The blade of the Airtraq is disposable. One study published in 2007 in *Anesthesiology* showed a 100% success rate at first attempt when using manual inline stabilization [2].

2) The A. P. Advance Video-laryngoscope (Venner Medical SA, Singapore) is based on a standard Macintosh laryngoscope that can be used as a stand-alone direct laryngoscope, or as a video-laryngoscope with a monitor attached to the handle and includes a “difficult airway” blade. A manikin study showed short intubation times for certified paramedics with the A.P. Advance [3], but large adequately powered, randomized controlled trials in difficult airway scenarios are lacking.

3) The C-MAC (Karl Storz, Tuttlingen, Germany) features size 2, 3 or 4 Macintosh blades or a “D”-blade (Difficult Airway Blade). The D-blade failed at first attempt in 30% of patients who showed a Cormack-Lehane grade 3 or 4 in a study by the inventor of the design [4]. One study shows a 93% success rate with the C-MAC using size 3 and 4 blades, compared to 84% for direct laryngoscopy when using manual inline stabilization, but intubation took longer [5].

4) The GlideScope (Verathon Inc., Bothell, WA, USA) is a widely used non-guided video-laryngoscope consisting of a curved video blade (single-use or reusable) and a special stylet to be used with the tracheal tube. An observational study in 50 patients showed a 100% success rate of the GlideScope in a difficult airway model using stiff extrication collars [6]. It also reduced intubation times compared with the conventional Macintosh laryngoscope in patients under manual inline stabilization [7].

5) The King Vision (Kingsystems, Noblesville, IN, USA) features either a channeled or a regular, disposable blade size 3. To date, there are no randomized controlled trials available for this device.

6) The McGrath MAC (Aircraft Medical Lt., Edinburgh, UK) is a non-guided video-laryngoscope that features disposable blades. It has been developed from the McGrath Series 5. In a randomized controlled trial with patients with a Mallampati grade of ≥3, the McGrath Series 5 provided a better laryngeal view compared to the C-MAC, but intubation took longer and more intubation attempts where needed [8]. To date, there are no randomized controlled trials available for the McGrath MAC video-laryngoscope.

These optical intubation devices or video-laryngoscopes (VLS) have dramatically improved the quality of glottic visualization. Multiple studies have proven enhanced visibility but not necessarily faster intubation times. Interestingly, in a study on manikins simulating difficult airway with stiff collars, VLS was not superior to direct laryngoscopy, but the sample size was low [9]. Furthermore, while VLS improve visualization of the airway, it is important to realize that a good view of the laryngeal opening does not automatically lead to intubation success. For example, in a recent study, the C-MAC VLS showed a good view of the larynx in 95% of cases, but the actual success rate of the intubation was only 88% [10]. These different success rates cannot directly be compared since these studies were performed in different patient populations by different operators, in different settings regarding difficult airways, and with different outcome parameters. Most importantly, the majority of patients enrolled presented with a normal airway, or only manual inline stabilization was used to simulate a difficult airway. No study compared all these devices in the same setting, and no sufficiently powered study used extrication collars to adequately simulate a clinically important difficult airway situation.

### Specific aims of the study are

1) To investigate which VLS devices reach a clinically acceptable minimal first attempt success rate of 90% in a simulated difficult airway scenario (primary outcome). We assume this lower limit of “90% first attempt success rate” is the lowest tolerable success rate in a difficult airway scenario.

2) To compare primary and overall success rates, view on the tracheal opening and time until intubation with the help of the guided vs. unguided VLS devices.

3) To evaluate possible adverse events, complications and side effects.

According to these specific aims, we propose the following hypotheses:

1) For our primary outcome, we assume that the lower limit of the 95% confidence interval (95% CI) of the first attempt success rate is not lower than 90%. The null hypothesis states that the 95% CI of first attempt success rate is below 0.9.

2) Successful tracheal intubation takes more time using unguided VLS compared with the other VLS devices that guide the tube towards the tracheal opening. The secondary null hypothesis states that there is no statistically significant difference in time until intubation success between a guided and an unguided VLS (two-sided). Other secondary outcome-hypotheses include that the overall attempt success rates are higher in guided VLS compared with unguided VLS.

3) Minor airway injury rates are within a maximum of 10% comparing guided vs. unguided VLS. The null hypothesis states that the differences of minor airway injury rates are higher than 10%.

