### Statistical analysis

For the primary outcome, it will be analyzed for each laryngoscope whether the 95% confidence interval of its primary success is below 0.9. For the secondary outcome parameters, the data distribution will determine which statistical test will be used. For frequencies (for example, number of required manipulations, overall attempt success, complications) chi-square test or Fisher’s exact test will be used. Parametric data will be analyzed using ANOVA; for non-parametric continuous data Kruskal-Wallis test will be used. For comparison between two devices, we will use Student’s *t*-test and Mann-Whitney’s *u*-test, as appropriate. We will do *a priori* comparisons of the time necessary until success between the unguided VLS and any of the guided VLS.

Data will be presented as mean with standard deviation, median and interquartile range, or number and percent. Effect sizes (with 95% CI) will be reported as Cohen’s d for interval data and as odds ratio for proportions. A probability of 0.05 is considered as statistically significant.

The patient flow diagram according CONSORT guidelines is provided in Figure 1.

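### Hypothesis 3 sets an equivalence null for minor airway injury, but the stated chi-square/Fisher test and odds ratio cannot reject that null

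*Protocol article*

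**What the plan says.** Under the specific aims, the third hypothesis of the protocol article reads "Minor airway injury rates are within a maximum of 10% comparing guided vs. unguided VLS". Its null follows at once: "The null hypothesis states that the differences of minor airway injury rates are higher than 10" per cent. The null is therefore a difference beyond a margin, and the claim to be supported is a difference inside it.

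The Statistical analysis section has no sentence devoted to this hypothesis. Its rule for frequencies is "For frequencies (for example, number of required manipulations, overall attempt success, complications) chi-square test or Fisher’s exact test will be used". On effect measures it says "Effect sizes (with 95% CI) will be reported as Cohen’s d for interval data and as odds ratio for proportions", and on significance "A probability of 0.05 is considered as statistically significant". It mentions no margin for injury, no risk difference with an interval, no shifted null and no equivalence rule.

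The Sample size calculation section covers the primary outcome and time to intubation. It gives no injury rate and no power for hypothesis 3.

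**The concern.** A chi-square or Fisher test starts from a null of zero difference. A small p-value shows that some difference exists, and a large one shows only that none was detected. Neither says whether the difference is larger or smaller than 10 points. The hypothesis as written can be supported only by rejecting a difference beyond the margin, and no p-value from the stated tests does that.

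The odds ratio does not fill the gap, because a fixed absolute margin matches no single odds ratio unless the base rate is known.

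At stake is the conclusion on one of the three numbered hypotheses, and the only one about safety. The test and the hypothesis can disagree both ways: a sizeable excess may go undetected, and a difference well inside the margin may be statistically significant.

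**Working it through.** **Inputs**

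- Margin: 10%, from hypothesis 3, read as absolute percentage points. The article does not label it absolute or relative, so this is an interpretation.
- Groups: "three video-laryngoscopes with a guiding channel for intubation" against three without, so the classes are 1:1 when pooled.
- Size: 107 evaluable per device (Sample size calculation), so 3 × 107 = 321 per class. With all 720 enrolled, 360 per class.
- Level: 0.05.
- Injury rates: not in the document. Assumed here from 2% to 50%.

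The article states no figure for hypothesis 3, so there is none to reproduce.

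**1. The two nulls side by side**

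- Hypothesis 3: H0 is |p_guided − p_unguided| > 0.10.
- Chi-square or Fisher: H0 is p_guided = p_unguided.

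The second null lies inside the region that hypothesis 3 wants to establish. Failing to reject it is not evidence against the first.

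**2. The odds ratio**

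OR = [(p + 0.10)/(0.90 − p)] / [p/(1 − p)]. A 10-point difference gives 3.35 at p = 5%, 2.25 at 10%, 1.71 at 20% and 1.50 at 40%. No one odds-ratio limit stands for the margin.

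**3. Two illustrative data sets (321 per class)**

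- 13 vs 26 injuries (4.0% vs 8.1%): chi-square p = 0.032. The risk difference is 4.0 points with standard error √(p1(1 − p1)/321 + p2(1 − p2)/321) = 1.88 points, so the 90% interval is 4.05 ± 1.645 × 1.88 = 1.0 to 7.1. The test is significant, and the protocol's null is rejected.
- 64 vs 80 injuries (19.9% vs 24.9%): chi-square p = 0.13. The difference is 5.0 points, standard error 3.29, 90% interval −0.4 to 10.4. The test is not significant, and the protocol's null is not rejected.

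**4. True difference exactly 10 points, 321 per class**

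Chi-square is non-significant when |d| < 1.96 × √(2p̄(1 − p̄)/n). For 20% vs 30% the threshold is 1.96 × √(2 × 0.25 × 0.75/321) = 0.0670. The standard error of d is √((0.16 + 0.21)/321) = 0.0340, so the probability is about Φ((0.0670 − 0.10)/0.0340) = Φ(−0.97), or roughly 0.17. Summing the binomial probabilities exactly gives 0.163. All scenarios, exact:

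| True rates | Chi-square non-significant | 90% CI inside ±10 points |
|---|---|---|
| 5% vs 15% | 0.8% | 5.5% |
| 10% vs 20% | 5.1% | 5.2% |
| 20% vs 30% | 16% | 5.0% |
| 30% vs 40% | 24% | 5.1% |
| 40% vs 50% | 27% | 5.0% |

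The middle column is an error rate only if non-significance is taken as equivalence.

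**5. True difference inside the margin**

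At 2% vs 6%, chi-square is significant in 76% of trials, while the 90% interval lies within ±10 points in 98%.

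**6. Power of the interval rule with no true difference**

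Power ≈ 2Φ(0.10/SE − z) − 1, with SE = √(2p(1 − p)/n) and z = 1.645 (90% interval) or 1.96 (95% interval). For p = 20% and n = 321, SE = 0.0316 and power = 2Φ(3.17 − 1.645) − 1 = 0.87. Exact values:

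| Common rate | 90% CI, n = 321 | 95% CI, n = 321 | 90% CI, n = 360 |
|---|---|---|---|
| 10% | 99% | 97% | 99% |
| 20% | 87% | 77% | 91% |
| 30% | 74% | 58% | 80% |
| 40% | 65% | 46% | 73% |

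**The case against.** The Statistical analysis section never names minor airway injury. The chi-square/Fisher rule reaches it through an illustrative list, and a margin analysis may exist in a fuller document. This stands in part: the assignment is by default, not by express statement. But injury is a frequency, complications are a listed example, and the article offers no other route. It states the null itself, so the mismatch lies within its own text.

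A reader might infer that a non-significant test will be reported as equivalence, or a significant one as a breach of the margin. The article states no such rule, so the error rates in step 4 are conditional on it. Likewise, a significant result at 2% vs 6% correctly detects a real difference. It misleads only if taken as an answer to hypothesis 3.

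A reader might also infer that the planned test would often miss a 10-point excess. That depends on injuries being common. At base rates of 5% and 10%, chi-square is non-significant no more often than the interval rule falsely concludes equivalence.

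Finally, pooling three devices per class is the natural reading of the hypothesis, but nearby text also speaks of single guided and unguided devices. Compared device by device (107 each), power of the 90% rule falls to 58% at a 10% injury rate and 16% at 20%.

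**Conclusion.** The point holds. Hypothesis 3 is an equivalence hypothesis, and the stated analysis cannot reject its null. That conclusion needs no assumption about injury rates.

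The size does need assumptions. If non-significance were read as equivalence, the wrong conclusion at a true 10-point difference would range from about 1% to 27% of trials as the lower rate goes from 5% to 40%, against about 5% for the 90% interval rule. This assumes pooled classes of 321 and an absolute margin.

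It should be fixed but is not critical. A reader might conclude that the trial's whole safety assessment is unsound. The document does not support that: the third aim is a broad evaluation of adverse events, and counts and percentages are to be reported, so the risk difference could be recovered from them. The primary outcome and the sample size do not depend on this hypothesis.

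**What to change.** State in the hypothesis that the margin is 10 percentage points, absolute. In the Statistical analysis section add one rule for hypothesis 3: estimate the pooled guided-minus-unguided risk difference, and conclude equivalence only if its 90% confidence interval (two one-sided 5% tests) lies wholly between −10 and +10 points. Report it beside the odds ratio. Keep chi-square or Fisher for frequencies that carry no margin.

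The cost is a sentence or two of text and no new data. Fewer than 10 patients had been enrolled at submission, so the rule could be set before results existed.

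The downside is power. At 321 per class with no true difference it exceeds 80% up to an injury rate of about 20%, then falls to 74% at 30% and 65% at 40%, so equivalence may not be shown if injuries are common. A 95% interval would be stricter, with power of 77%, 58% and 46% at rates of 20%, 30% and 40%. The level should therefore be fixed in advance.

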## Methods/design

### Study design

The SWIVIT trial is a prospective, patient-blinded, multicenter, randomized controlled trial at the anesthesia departments of the University Hospital of Bern, the University Hospital of Lausanne and the University Hospital of Geneva, all in Switzerland.

### Patient population

With ethics committee approval (KEK Bern ref. nr. 106/12 on 11 September 2012; Chairperson: [name]. [name]) and written informed consent, we will include adult patients of both genders, ASA (American Society of Anesthesiologists) physical status I to III, and scheduled at one of the participating hospitals for elective surgery under general anesthesia requiring tracheal intubation.

Patients are not eligible if they are at risk for aspiration (non-fasted, severe gastro-esophageal reflux disease, hiatal hernia), with known or presumed difficult airways (body mass index >35 kg/m^2^, Mallampati >III, thyromental distance <6 cm, interincisor distance <3.5 cm [11], known difficult mask ventilation or difficult laryngoscopy, or scheduled for awake tracheal intubation), or if they refuse to participate or are unable to give informed consent.

### Sample size calculation

Most previous studies have based sample size calculations on differences of the intubation difficulty score (IDS), developed by Adnet in 1997 for direct laryngoscopy [12]. However, a retrospective study by McElwain has raised concerns about the validity of the IDS with VLS [13]. The most important outcome parameter for VLS or any guided intubation devices is the success rate. Most available data are from patients with normal airway anatomy and, therefore, not comparable with our setting. Only one study immobilized the patients’ necks with collars to investigate the C-MAC in 43 patients. That study found an overall success rate of 88% [10]. This is an unacceptable low success rate for the management of a difficult airway, but the study was underpowered: we calculated the 95% CI in that study to be 0.75 to 0.95 for overall success rate.

In order to rate an intubation device as “successful”, we define that the lower limit of the 95% CI should not be smaller than 0.9. We based our sample size on these values, congruent with our findings in a small pilot sample. We calculated the necessary sample size to obtain a distance of 0.05 to the expected success rate of 0.95, provided a probability of 0.95 and a power of 80% (SAS v.9.1, SAS Institute Inc., Cary, NC, USA). A total of 107 patients per device are necessary for this lower limit of 0.9. A total of 642 (6 × 107) patients will be necessary based on these assumptions, which leads us to include 720 patients to compensate for dropouts or missing data.

Secondary endpoints include parametric data, such as time necessary until success. Time until success has varied widely among different devices in published studies. Furthermore, that parameter seems to be influenced by the anesthesia provider. Therefore, we based our sample size calculation on first attempt success rate.

Because available data about our primary outcome, the first attempt success rate in a simulated difficult airway scenario, are scarce, we will recalculate sample size after the first 120 patients, based upon the values obtained from the first 20 patients for each device. In order to reduce bias, all participating investigators will remain unaware of results obtained from these 120 patients.

We will compare time to intubate in unguided vs. guided VLS as the secondary outcome. There are not sufficient data available to calculate sample size for this secondary outcome parameter. Therefore, we base our sample size calculation on effect size: based on an estimated medium effect size (Cohen’s d of 0.5; assuming normal distribution), 64 samples per group are necessary, given a 0.05 level (*P* = 0.05) and 80% power. Because our primary outcome requires 107 patients per group, we are well within the necessary sample size even for this secondary outcome parameter.

Experience with the device is expected to be a major confounding factor. Only a limited number of experienced anesthesiologists at each study center will perform the intubation. To avoid a learning curve bias and to minimize variation in the performance, only anesthesiologists who have intubated patients without any airway pathology several times with each device until they feel competent with the devices will participate. We did not set *a priori* a fixed figure of intubations for each device because the individual experience with different devices is very divergent between the study centers and the participating anesthesiologists. Ideally, experience with the device should be equal, and prior experience will be recorded. We limit participants per center to a maximum of four physicians.

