### Potential problems and limitations

Because sample size has been calculated based on relatively vague figures, some adjustments in the total, necessary sample size may have to be incorporated when we re-calculate our sample size after the first 120 patients as per protocol. However, the statistical calculation is sound, and our assumptions are based on highly probable clinical expectations. Furthermore, the results of our study will be of clinical relevance regardless of whether our primary hypothesis will be confirmed or not and the much-feared “negative results” should be of no concerns in this study.

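### 107 patients per device do not give the stated 80% power for a lower 95% limit of 0.9 at a true success rate of 0.95; exact power is about 38% to 71%, depending on the interval.

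*Protocol article*

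**What the plan says.** The Sample size calculation section of the protocol article sets the pass rule for a device: "we define that the lower limit of the 95% CI should not be smaller than 0.9". The abstract words the same rule as "lower limit of the 95% confidence interval >0.9". The calculation was made "to obtain a distance of 0.05 to the expected success rate of 0.95, provided a probability of 0.95 and a power of 80" per cent, and its result is "A total of 107 patients per device are necessary for this lower limit of 0.9". Six devices at 107 make 642. This is raised to 720 (120 per device) to cover dropouts and missing data.

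The Statistical analysis section applies the rule to each laryngoscope separately. The sample size is to be recalculated after the first 120 patients, 20 per device.

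Two statements lean on the calculation. The abstract says "Because of the sufficiently powered multicenter design this study will deliver important and cutting-edge results". Potential problems and limitations concedes that the inputs are vague and that the total may change, but adds: "However, the statistical calculation is sound, and our assumptions are based on highly probable clinical expectations".

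**The concern.** For a rule of this kind, power is the chance that a device with the assumed true rate produces a lower limit of at least 0.9. That is a stricter demand than getting an interval of a certain width around an estimate of 0.95. If the true rate is 0.95, the observed rate falls below 0.95 about half the time, so the interval must be clearly narrower than 0.05 on its lower side for the rule to be met in 80% of trials. A sample of 107 looks too small for that.

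At stake is how a miss is read. If the trial is believed to have 80% power, a device that fails the benchmark looks inferior. If the power is much lower, a miss says little about a device that truly succeeds in 95% of patients, and two equally good devices can easily get opposite verdicts.

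**Working it through.** **Inputs (Sample size calculation).** Benchmark 0.90; assumed true rate 0.95; 95% confidence; stated power 80%; n = 107, or 120 if nobody is lost. Neither the type of interval nor its sidedness is given, so the usual options are all tried.

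**1. Trying to reproduce 107.** Normal-approximation sample sizes for 80% power:
- Variance at 0.95, n = (z_α + z_β)² × 0.95 × 0.05 / 0.05². One-sided: (1.645 + 0.842)² × 19 = 117.5, so 118. Two-sided: (1.960 + 0.842)² × 19 = 149.1, so 150.
- Null and alternative variances, n = (z_α × √(0.9 × 0.1) + z_β × √(0.95 × 0.05))² / 0.05². One-sided: 183.3, so 184. Two-sided: 238.0, so 239.

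None gives 107. It is, however, the smallest n at which a one-sided 95% Clopper-Pearson lower limit reaches 0.9 when the *observed* rate is 0.95 (0.89974 at n = 106, 0.90005 at n = 107). That calculation has no power term. Whether it is the source of 107 is only a guess.

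**2. Successes needed at n = 107.** The smallest x whose lower limit is at least 0.9:

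| 95% interval | Limit at x − 1 | Limit at x | x needed |
|---|---|---|---|
| Wilson, two-sided | 0.8952 | 0.9078 | 103 |
| Agresti-Coull, two-sided | 0.8925 | 0.9047 | 103 |
| Clopper-Pearson, two-sided | 0.8943 | 0.9070 | 103 |
| Jeffreys, two-sided | 0.8881 | 0.9006 | 102 |
| Wald, two-sided | 0.8877 | 0.9003 | 101 |

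A one-sided 95% limit needs 102 (Wilson, Agresti-Coull, Clopper-Pearson, Jeffreys) or 101 (Wald). No limit falls exactly on 0.9, so it does not matter whether the rule reads *at least* or *above*.

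**3. Exact power at a true rate of 0.95.** With failures distributed Binomial(107, 0.05), the probabilities of 0 to 6 failures are 0.0041, 0.0233, 0.0649, 0.1196, 0.1637, 0.1775 and 0.1588.
- At least 103 successes (up to 4 failures): the first five terms give 37.6%.
- At least 102 (up to 5 failures): 0.3757 + 0.1775 = 55.3%.
- At least 101 (up to 6 failures): 0.5532 + 0.1588 = 71.2%.

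The 71.2% has a price: the rule of 101/107 also passes a device with a true rate of exactly 0.90 in 8.1% of trials, against a nominal 2.5% for a two-sided 95% interval. The rule of 103/107 passes such a device in 1.5%.

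**4. Which interval is likely.** The same section reports 0.75 to 0.95 for an 88% success rate in 43 patients. For 38/43, Agresti-Coull gives 0.751 to 0.954 and Wald 0.788 to 0.980. The article's own interval therefore fits Agresti-Coull and not Wald, which points to about 38%.

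**5. If all 120 per device are analysed.** Two-sided non-Wald intervals need 115/120: 44.2%. Two-sided Wald, or one-sided non-Wald, needs 114: 60.6%. One-sided Wald gives 74.8%.

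**6. What would give 80%.** With a two-sided interval, power stays at or above 80% from about 254 per device (Wilson), 255 (Clopper-Pearson) or 186 (Wald). Alternatively, with the rule of 103/107, the true rate would have to be about 97.1%.

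**7. Power at other true rates, two-sided Wilson, Agresti-Coull or Clopper-Pearson.**

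| True rate | n = 107 | n = 120 |
|---|---|---|
| 0.95 | 38% | 44% |
| 0.97 | 78% | 85% |
| 0.98 | 94% | 97% |

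**8. Opposite verdicts for two devices, both at 0.95.** 2 × power × (1 − power): 2 × 0.376 × 0.624 = 47% at n = 107. With Wald, 2 × 0.712 × 0.288 = 41%.

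**The case against.** The best defence is that 107 is a precision target with a loose label. The text speaks of a distance of 0.05, and at n = 107 the Wilson half-width is at most 0.05 with 83% probability. This may explain the number, but it does not support the claim. The section ties 107 to the lower limit of 0.9, and the primary analysis tests that limit. Controlling the width does not control the chance of clearing 0.9.

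A second defence is that 107 and 720 are provisional, because the sample size is recalculated after 120 patients and the vague inputs are admitted. That is true, and N should not be treated as fixed. But the recalculation is described as updating the values obtained from the first 20 patients per device. It does not correct the method.

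Three stronger readings are tempting and go too far:
- *A device with 95% success will fail more often than it passes.* At n = 107 this holds for two-sided Wilson, Agresti-Coull and Clopper-Pearson intervals, but not for Jeffreys (55.3%), Wald (71.2%) or a one-sided limit. The article does not fix the interval.
- *The trial can hardly ever confirm its hypothesis, because all six devices must pass.* The abstract states "The working hypothesis is that each video-laryngoscope provides at least a 90% first intubation success rate", but the specific aims ask which devices reach the benchmark and the analysis is per device. No joint test is planned, so any all-six probability (0.376⁶ = 0.3%, for instance) is illustrative only.
- *Leaving the interval unnamed is itself a defect.* An article may leave this to a full protocol or analysis plan that is not shown. It matters here only because no usual choice yields 80%.

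**Conclusion.** The stated 80% power is wrong. For the stated pass rule, at 107 per device and a true rate of 0.95, exact power is 37.6% to 71.2% across the usual intervals. About 38% is the best-supported figure, given the article's own worked interval. The dropout allowance does not rescue it: even with no losses, power at 120 is 44.2% to 74.8%.

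The shortfall rests only on inputs printed in the article and on independent binomial outcomes within each device. The 38% additionally assumes a two-sided non-Wald interval. Where 107 came from is not established and does not affect the conclusion. The design can still detect very good devices: it has adequate power at true rates of about 0.97 to 0.98, but not at the 0.95 on which it was planned.

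**What to change.** - Name a non-Wald interval, such as Wilson or Clopper-Pearson, and replace the 80% with the power it gives: with 107 (120) analysed per device, 38% (44%) at a true rate of 0.95, 78% (85%) at 0.97 and 94% (97%) at 0.98.
- Base the recalculation after 120 patients on the same quantity, the probability that the lower limit reaches 0.9, so that the error is not repeated.
- For a device at 95%, withdraw the statements that the design has sufficient power and that the calculation is sound.
- State in advance that a device missing the benchmark is reported as *not shown to reach 90%*, and that one device passing while another fails is not evidence that the two differ.

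This is rewording and needs no extra patients. The cost is a less favourable stated power. Keeping the 80% claim at 0.95 would instead take about 255 evaluable patients per device (Clopper-Pearson), or 6 × 255 = 1,530 in all. Fewer than 10 patients had been enrolled at submission (Trial status), so the correction could be made before any results are known.
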